## Abstract

Recent evidence suggests that the development of gut microbiota during infancy affects several metabolic, immune, and endocrine pathways in humans. An imbalance in gut microbiota diversity or function, also known as dysbiosis, not only affects early child growth and development, but is also linked with the development of chronic, non-communicable diseases in later life. The
**C**hild
**H**ealth
**A**nd
**M**icrobiome Development Study –
**P**akistan (CHAMP) study aimed to longitudinally assess gut microbiota development and associated factors (maternal, child, and demographic) during early childhood in populations residing in malnutrition-endemic communities in Pakistan. A prospective cohort of mother-infant pairs (n=70) will be recruited from District Swat, Pakistan, and followed for two years. Complete information about demographic characteristics, anti-natal and post-natal care, dietary intake, feeding practices, and child health will be collected at baseline and 3, 6, 12, 18, and 24 months. Anthropometric measurements (height, weight, mid-upper arm circumference, and head circumference), dry blood spots, and fecal samples were also collected. Ethical approval for the study was obtained from Khyber Medical University, Pakistan. The study is also registered on
clincaltrial.gov (Ref no: NCT05793294). The study findings will help researchers understand gut microbiota development, associated factors, and their impact on longitudinal growth in infants during the first two years of life.

## Introduction

Infancy, the period from birth to around two years of age, is a crucial stage in human development, characterized primarily by rapid physical, mental, and emotional growth.
^
1
^ During this period, many environmental factors such as gestational age, sex, ethnicity, dietary intake, nutritional status, and socioeconomic conditions significantly affect child growth, development, and overall health.
^
2,
3
^ However, to date, these factors, either alone or synergistically, have failed to explain the overall spectrum and variations in children. Recent studies have emphasized that apart from the intersection of environmental factors, the gut microbiome also plays an important role in mediating growth and development, especially during infancy.

The human fetus is believed to develop in a microbe-free environment.
^
4
^ However, immediately after birth, the infant gut, especially the distal ileum and colon, is rapidly colonized by different microorganisms (bacteria, fungi, archaea, and viruses) via vertical transmission from maternal body sites such as the vagina, skin, oral cavity, and gut.
^
5
^ In newborn infants, the gut microbiota exhibits low diversity, consisting mainly of facultative anaerobic bacteria, such as
*Proteobacteria* (e.g.,
*Escherichia* and
*Enterobacter*) and
*Firmicutes* (
*Staphylococcus*,
*Enterococcus*and, and
*Streptococcus*).
^
6
^ Early colonization has a profound influence on the gut environment and subsequent colonization by obligate anaerobes, such as
*Bifidobacterium, Bacteroides* and
*Clostridium.* The relative abundance of
*Bifidobacteria* gradually increases 3 – 4 days after birth and becomes a predominant bacterial genus when the baby is approximately 1 month old.
^
7,
8
^ In healthy growing children, the gut microbiota gradually increases in complexity with a highly diverse microbial composition during and after the first two–three years of life.
^
9
^ During this period, the patterned ecological assembly of microbes occurs mainly under the influence of delivery mode, type of feeding, complimentary feeding practices, antibiotic use, and geography.
^
9–
12
^ Gut microbiota development during early life affects several metabolic, immune, and endocrine pathways and is thus intimately linked to child growth and development.
^
13
^ Therefore, any disturbances in the host-microbe coevolution, microbial composition, or functional potential of the gut microbiome, commonly referred to as microbial dysbiosis, can impair immune function, growth, and development in children.

In recent years, several studies have reported associations between gut microbiome dysbiosis and impaired growth and development in children from different countries across the word. For example, a causal relationship between gut microbiome immaturity, undernutrition, and impaired growth has been reported in 6-
and 18-months old children.
^
14
^ Similarly, a Swedish cohort encompassing 471 children has also reported significantly lower microbial diversity and reduced abundance of
*Faecalibacterium* and
*Ruminococcus* in the gut microbiome of children with slower weight gain compared to normal children.
^
15
^ Research studies from developing countries, where malnutrition is common, have also reported impaired or immature gut microbiome in malnourished (stunting, wasting, and underweight) children compared to that in healthy controls. In Bangladesh, children with severe acute malnutrition (SAM) exhibit a considerably less diverse gut microbiome, low relative abundance of
*Bacteroidetes* and high relative abundance of
*Proteobacteria* especially the pathogen/pathobiont genera such as
*Klebsiella, Escherichia, Shigella*, and
*Streptococcus*.
^
16
^ In another study of a group of SAM infants aged 6–24 months, the absolute abundance of
*B. infantis* was considerably lower than that of age-matched healthy infants.
^
17
^ These findings were also confirmed by studies conducted in other developing countries in Asia and Africa.
^
18–
20
^ Altogether, these findings suggest that an immature/poorly developed gut microbiome in infants and young children is associated with malnutrition and its consequences, particularly impaired growth and development. As a result, a nutritional intervention strategy that does not consider the gut microbiome will fail to ameliorate the long-term consequences of malnutrition, including child health and cognitive development.
^
21
^ Clinical studies in animals and humans have already demonstrated the positive impact of microbiome-based nutritional interventions on the gut microbiome and ponderal growth.
^
22,
23
^ These findings may have important implications for low- and middle-income countries such as Pakistan, where malnutrition in children is a crucial public health challenge.

Pakistan is the 5
^th^ most populous country in the world (approximately 250 million people)
^
24
^ with enormous economic, geopolitical, social, and poverty-related challenges.
^
25
^ According to the latest national nutrition survey, the prevalence of stunting (40.2%), wasting (17.7%), and micronutrient deficiencies in children under five years of age
^
26
^ remained unacceptably high. Over the last five years, the country has been placed in the “Serious” category of the Global Hunger Index.
^
27
^ The consequences of malnutrition are also economically catastrophic with $7.6 billion/annum (~3% of GDP) lost to malnutrition.
^
28
^ Over the last two decades, there has been virtually no improvement in the overall nutritional status of the Pakistani population, despite efforts from the government and developmental organizations. Without coordinated efforts, it is very unlikely that Pakistan will achieve the UN Sustainable Development Goals to end hunger and all forms of malnutrition by 2030.
^
29
^ Successful tackling this issue requires cost-effective, culturally relevant, and sustainable nutritional interventions. Keeping in mind the central role of the gut microbiome in mediating malnutrition in children, it is crucial to map the compositional and functional dynamics of the gut microbiome and associated maternal, child, and environment-related factors during early childhood in populations residing in malnourished communities in Pakistan. Therefore, the current study attempts to characterize how the gut microbiome develops in a cohort of children at high risk of malnutrition in the Khyber Pakhtunkhwa province of Pakistan.

## Protocol

### Objectives

The primary objective of the CHAMP study is to characterize gut microbiota development and longitudinal growth in infants during the first two years of life. This will be done by assessing the microbial diversity, relative abundance of the dominant microbiota, and interindividual variations in microbial diversity and infant growth patterns. The secondary objective of the study is to investigate the impact of (i) sociodemographic characteristics, (ii) mode of delivery, (iii) maternal factors such as diet and anti-natal and post-natal care, (iv) child dietary intake and feeding practices, and (v) nutritional status of the child on gut microbiota composition at different time points from birth until the child is two years old.

### Operational definitions

•
**Nutritional status:** The nutritional status of the child will be measured in terms of weight for age (WAZ), height for age (HAZ), and weight for height (WHZ) according to the WHO reference range.
^
30
^
•
**Underweight:** Defined as weight for age of the child below two standard deviations (-2SD) from the median weight for age of the reference population.•
**Stunting:** Child height for age below minus two standard deviations (-2SD) from the median height for the age of the reference population.•
**Wasting:** Child weight for height below minus two standard deviations (-2SD) from the median weight for height of the reference population.

### Study design and setting

The CHAMP study is a population-based, prospective cohort study involving mother-infant pairs (dyads) from District Swat, Pakistan. Swat is located at 34°46′58″ N and 72°21′43″ N in Khyber Pakhtunkhwa province of Pakistan and is home to more than 2.3 million people.
^
31
^ Because of its geographic location in the Hindukush–Himalayan region, most of the land is occupied by mountains and thick forests. The area is one of the most marginalized and neglected regions of the province, with livestock, agriculture, horticulture, and tourism as the primary sources of income and livelihood of the local population.
^
32
^ Swat is among the most vulnerable districts in Pakistan and is prone to climate change. Since 2010, the district has been hit by at least three major floods that have significantly disrupted essential services, such as healthcare, sanitation, and access to safe drinking water.
^
33
^ As a result, the majority of the population, especially children, are at a high risk of malnutrition and its deleterious consequences.

Administratively, the district is divided into seven administrative units known as Tehsil Municipal Administration units (TMAs). Tehsil Matta was chosen as the study area because it is the second most populated tehsil in Swat district, with the highest number of rural and remote communities. Following a preliminary survey, UC Beha was selected as the study site for several reasons. It is located at a high altitude with the longest adjoining borders with district Dir (Upper), and most of the population lives in agropastoral communities with very limited access to education and healthcare facilities. In winter, access to the area is limited by heavy snowfall and landslides.

### Sampling technique

District swats are divided into seven administrative units known as Tehsil Municipal Administration units (TMAs). Of these, tehsil Matta was chosen as the study area because it is the second most populated tehsil in Swat district, located at a high altitude with the longest adjoining borders with Dir district (Upper), which has the highest number of rural and remote communities. The Matta tehsil is further divided into union councils, which are the primary administrative institutions in Pakistan. In rural areas, union councils are referred to as village councils. Of the 13 village councils in the sampling area, three union councils will be randomly selected as the primary sampling unit. Subsequently, the researchers visited the primary health centers and designated vaccination centers within the chosen village councils. Newborn children will be identified using the Extended Program for Immunization (EPI) register. Potential participants will be appraoched with the help of Lady Health Workers (LHWs), community-based health workers linked to local health facilities. All families in the area are registered with a designated LHW who regularly visited them. Important information, such as the child’s name, father’s name, date of birth, and address, will be recorded, and a list of eligible study participants will be prepared. Once recruited, each participant will be followed up for two years. The study follows ethical principles involving human subjects as outlined in the declaration of Helsinki. Ethical approval for this study was granted by the Ethics Board of Khyber Medical University, Pakistan ref no DIR/KMU-EB/BR/001-03 dated 11/01/2024.

### Participants selection

The study population will include 70 mother-infant pairs (dyads), according to the following criteria:

Inclusion criteria
•Apparently healthy infants of both genders aged 0 – 28 days•Born by natural or caesarean delivery•Born to parents from district Swat•Parents/caregivers have no plans to move out of the stud site for at least two years after enrollment in the study.

The exclusion criteria are:
•Child born to an underage (<18 years old) mother.•Infants born with severe acute or chronic medical conditions that require hospitalization, prolonged use of medication, or both, or diagnosed with enteropathies.•Weight of the child is <1500 gm.

Ethical approval for the study was granted by the Research Ethics Board of Khyber Medical University. This study was also registered at
www.clinicaltrial.gov (NCT05793294).

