### Data analysis

The raw sequencing data will be processed using metapi pipeline (
https://github.com/ohmeta/metapi) followed by quality control process using standards for filtering and trimming the reads (average Phred quality score ≥ 20 and length ≥ 30) using fastp v0.20.1 . Human reads will be removed using Bowtie2 2.4.2 (human genome GRCh38). Taxonomic profiling of the samples will be performed using Kraken2 with standard bacterial, viral, and eukaryotic databases. Diversity assesment will be performed using the MicrobiotaProcess package. Differences in the alpha diversity will be estimated using the Wilcoxon rank sum test. Bidimensional visualization (Beta diversity) will be measurted using non-metric multidimensional scaling and the Bray–Curtis dissimilarity metric implemented in MicrobiotaProcess packages for GNU/R. The ADONIS function was used for obtaining differences in the taxonomic compositions between the groups. Assessment of the differentially abundant species will be done using the metagenomeSeq package.
^
30
^ An adjusted p-value ≤ 0.05 will be considered statistically significant.

We will seek to identify any correlations between the collected metadata and microbiome composition, and identify any gutmicrobiota trends associated infant demographic characteristics, dietary intake (IYCF data), nutritional status (weight for height, weight for age, and height for age and BMI for age z-score, MUAC and head cicrumference) health record (history of diarrhea, upper respiratory tract infections, antibiotic use and duration etc). We will also decorticate the changes in infant gut microbiome in relation to mother dietary intake data (collected though DQQ) and nutritional status (BMI). All postprocessing and statistical analyses will be performed in R.

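### Preterm infants are eligible, but gestational age is in no listed data item or analysis and no corrected-age rule is given, so early birth may confound the nutritional-status and delivery-mode associations with the microbiome

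*Protocol article*

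**What the plan says.** **Eligibility (Participants selection).** Infants enter on postnatal age and apparent health: "Apparently healthy infants of both genders aged 0 – 28 days". Two exclusions bear on early birth. One is weight, "Weight of the child is <1500 gm", without saying whether this is at birth or at enrolment. The other is illness: "Infants born with severe acute or chronic medical conditions that require hospitalization, prolonged use of medication, or both, or diagnosed with enteropathies". Neither list contains a gestational-age limit.

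**Growth scoring (Operational definitions).** Weight-for-age, height-for-age and weight-for-height are taken against the WHO reference. Stunting, for example, is "Child height for age below minus two standard deviations (-2SD) from the median height for the age of the reference population". The section does not say whether age is chronological or corrected. Date of birth, under Sampling technique, is the only source of age that is listed.

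**Gestational age.** It appears once, in the Introduction: "many environmental factors such as gestational age, sex, ethnicity, dietary intake, nutritional status, and socioeconomic conditions significantly affect child growth". It is not named in the Objectives, in Data collection or in Data analysis. Data analysis plans to "identify any gutmicrobiota trends associated infant demographic characteristics, dietary intake (IYCF data), nutritional status" and other recorded characteristics. Its named test for alpha diversity is the Wilcoxon rank sum test, and ADONIS is described as a comparison between groups.

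**Timing.** Sociodemographic, antenatal and postnatal care data are taken at baseline only. Study status reports baseline complete for all 70 infants and 66 seen at 3 months, with the study running to May 2026.

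**The concern.** The article names a determinant of growth, admits infants who differ on it, and then does not carry it into any listed objective, data item or analysis. If z-scores use age since birth, an infant born early will tend to look short and light for age because of early birth rather than poor nutrition. If early birth also shifts the microbiota, infants classed as stunted or underweight will differ in microbiota for a reason other than malnutrition. The delivery-mode contrast is exposed in the same way if early birth is more common after one mode of delivery.

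Nutritional status and mode of delivery are both named factors in the secondary objective, and the Discussion wants the results to support future nutrition interventions. An association produced by early birth would misdirect that use.

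Timing makes this more than a matter of later analysis detail. If gestational age was not asked at baseline, a later analysis plan cannot create it.

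**Working it through.** The article gives no preterm rate, effect size or power calculation, so there is no planned figure to reproduce. The check has two parts.

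**1. The text**

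- Entry: no gestational-age limit. The health criteria remove some preterm infants but not well ones of 1500 g or more.
- Scoring: the issue touches weight-for-age and length-for-age, hence underweight and stunting. Weight-for-height, hence wasting, is not indexed by age.
- Adjustment: a Wilcoxon rank sum test takes no covariate, so the named alpha-diversity comparison cannot adjust for gestational age even if it was recorded. ADONIS can take further terms, but none is stated.

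**2. Possible size (every input is an assumption)**

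Let p be the preterm share, d1 the shift in z-score and d2 the shift in a microbiome measure, both in SD, with no true association otherwise. With v = p(1 − p), the induced correlation is

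r = v·d1·d2 / √[(1 + v·d1²)(1 + v·d2²)].

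For one two-sided 5% test at n = 70, with s = √67 · atanh(r), the rejection rate is Φ(s − 1.96) + Φ(−s − 1.96).

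Worked case, p = 0.10, d1 = 1.5, d2 = 1: v = 0.09; r = 0.135 / √(1.2025 × 1.09) = 0.118; s = 0.97; rejection rate about 16%.

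| Preterm share | Expected of 70 | d1 | d2 | Induced r | Rejection rate |
|---|---|---|---|---|---|
| 5% | 3.5 | 0.5 | 0.25 | 0.006 | 5.0% |
| 5% | 3.5 | 1.5 | 1 | 0.066 | 8.4% |
| 10% | 7 | 0.5 | 0.25 | 0.011 | 5.1% |
| 10% | 7 | 1.5 | 1 | 0.118 | 16% |
| 20% | 14 | 0.5 | 0.25 | 0.020 | 5.3% |
| 20% | 14 | 1.5 | 1 | 0.191 | 35% |

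If d2 = 0, then r = 0 in every row. For scale, |r| must reach 0.235 for significance at n = 70, and r = 0.33 is needed for 80% power.

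**By visit.** Take shift = months early × monthly length gain / SD, with 0.75 to 1.5 months early. The assumed gain and SD are 3 cm per month and 2 cm at 3 months, and 1 cm per month and 3 cm at 24 months.

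- 3 months: 0.75 × 3/2 = 1.1 to 1.5 × 3/2 = 2.25 SD. With p of 10% to 15% and d2 of 0.25 to 1, r is 0.02 to 0.21 and the rejection rate about 5% to 42%.
- 24 months: 0.75 × 1/3 = 0.25 to 1.5 × 1/3 = 0.5 SD. With the same p and d2, r is 0.006 to 0.06 and the rejection rate about 5% to 8%.

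Under these assumptions the problem is mainly one of the early visits. These rates are for a single nominal 5% test. The article applies an adjusted p-value, so they show direction and scale only.

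**The case against.** The best defence is that this is a condensed article. Covariate lists, corrected-age rules and sensitivity analyses usually sit in a fuller document. The Introduction is background and commits the authors to nothing. The data lists are open-ended, the items of the antenatal questionnaire are not shown, and Data Availability says the data collection questionnaire is deposited separately. If gestational age is in it, the plan to relate collected metadata to microbiome composition could cover it. The article also limits its conclusions to association, and a population-based cohort may reasonably include preterm infants.

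Much of this stands, and it rules out several stronger readings that a reader might infer:

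- *Gestational age was not collected.* The documents show only that it is not listed.
- *Infants are scored on uncorrected age.* This is the natural reading, since date of birth is the only listed age source, but the article does not say so.
- *The results are confounded.* That also needs a link from gestational age to the microbiota. The article's own list has the microbiota developing "under the influence of delivery mode, type of feeding, complimentary feeding practices, antibiotic use, and geography", which omits gestational age. For delivery mode, the link with early birth is likewise unstated.
- *Preterm infants would form a quarter to a third of the stunted group.* With 7 to 10 preterm infants and 28 stunted (40.2% of 70), 7/28 = 25% and 10/28 = 36%, so essentially all of them would have to be stunted. The 40.2% is also a national under-five figure, not a rate for early infancy.

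Three things survive. The article fixes an alpha-diversity test that cannot adjust. The baseline-only antenatal interview is already complete. The association-only caveat does not help a reader separate malnutrition from early birth.

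**Conclusion.** The point holds as a possible confounder that the plan, as written, neither measures visibly nor adjusts for. It concerns weight-for-age and length-for-age, underweight and stunting, and the delivery-mode contrast. It does not reach wasting through age scoring.

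The size cannot be determined from the documents. Under the assumed ranges it runs from nothing worth noting to a clear rise in false-positive findings at 3 months, and it is small by 24 months. No calculation was made for delivery mode. Without gestational age the investigators could not tell which case applies. The change is worth making because it is cheap, with medium confidence that it matters.

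**What to change.** - State whether gestational age and birth weight were recorded in the baseline antenatal questionnaire. If so, use them. If not, ask the mother for both at the next visit.
- State which age enters the z-scores, and keep chronological age for the main ones.
- Include gestational age as a covariate in the nutritional-status and delivery-mode analyses, as a term in ADONIS and in a regression model for alpha diversity reported alongside the Wilcoxon test.
- Repeat the growth-microbiome analyses (a) without infants under 37 weeks and (b) with corrected-age z-scores, and report whether the conclusions hold. Corrected age can be negative at the baseline visit (0 to 28 days), so say how that visit is handled in (b).

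**Cost.** One or two questions at most, one covariate and two reruns. Recalled gestational age is imprecise, so adjustment will be incomplete, and the extra covariate slightly widens intervals in a cohort of 70.
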